## Background

The health benefits of sport and physical activity (PA) have been studied extensively. The results demonstrate that participation in PA, which includes sporting activity, is associated with a reduced risk of over 20 health conditions, including cardiovascular disease and some cancers
[1, 2]. Targeting those with the greatest levels of inactivity will subsequently have an effect on all-cause mortality
[3] and produce the highest decrease in the incidence of chronic disease. In the most recent Cochrane review of interventions intended to increase physical activity
[4], the authors conclude that: "Nevertheless interventions which provide people with professional guidance about starting an exercise programme and then provide ongoing support may be more effective in encouraging the uptake of physical activity. There is no evidence that such interventions will reduce physical activity or cause other harm. There is only very limited evidence of the long-term effectiveness of interventions” (page 12).

Individuals report numerous barriers that impede their ability to be physically active
[5]. Lack of time and access to facilities are among the most common barriers that have been identified. “Exercise on prescription” interventions that involve a health professional’s written advice to a patient to be more physically active have been used with variable success
[6, 7]. A meta-analysis of the efficacy of gym-based exercise referrals for inactive people with medical conditions
[8] suggested that while these were effective the absolute health risk reduction was small due to patients failing to maintain activity levels over time. The authors show that, across the studies, 17 sedentary people would have to be referred for one person to become moderately active. They cite a range of barriers such as a lack of self-efficacy, poor body image, poor time management, lack of social support, intimidating environments, inadequate supervision and inconvenient opening hours as limiting the efficacy of these interventions.

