#### Research questions and hypotheses

The primary purpose of the trial is to test the independent and synergistic efficacy of the 12-week sports-oriented exercise referral intervention and the self-help web-based intervention intended to promote sustained and increased levels of physical activity over a period of 12 months. Do these interventions separately and in combination improve these indicators and do they improve them above that expected by existing gym-based GP referral alone? The secondary questions are whether these interventions improve other clinical indicators of cardiovascular health (for example, body mass index, waist and hip measures, blood pressure and other measures that contribute to the QRisk2 risk indicator) above that expected by existing gym-based GP referral? Do these interventions increase participation in sporting activity over a period of 12 months?

The interventions individually will be regarded as successful if they lead to an average increase in activity of 100 metabolic equivalent of task (MET)-minutes per week. This equates to engaging in an extra moderate intensity activity, say brisk walking (3.3 MET) for 30 minutes per week. The new interventions will be regarded as superior to the standard gym-based referral if they increase activity levels above those of the standard care gym-based exercise by 20 MET-minutes per week.

We will assess changes in indicators relating to cardiovascular health including blood pressure, weight, and waist and hip circumference. In terms of blood pressure, the interventions will be regarded as successful if they lead to an average decrease in blood pressure of 2.5 mmHg. We will assess the proportion of the sample reducing their blood pressure by more than 10 mmHg and an intervention will be regarded as a success if more than 20% of the members of that study arm achieve a reduction greater than this. The interventions will also be deemed to have been successful in promoting sports participation if they increase sports-related activity by 100 MET-minutes per week.

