## Methods/design

Participants will be inactive people aged 18 to 74 years who are eligible to be referred by their GPs for an exercise intervention. Participants will be people with hypertension or high-normal blood pressure and assessed as being inactive or moderately inactive using the General Practice Physical Activity Questionnaire (GPPAQ) screening tool. The inclusion and exclusion criteria are detailed below.

The study will be conducted in the Guildford and Waverley CCG area (Surrey, UK) and patients will be recruited via GP surgeries serving catchment areas within reasonable reach of Surrey Sports Park and the five DC leisure centres in Waverley, Surrey, UK. We have designed the study with the intention to allow recruitment for all patients eligible for an exercise referral within the 9 months of the proposed trial data collection phase.

The trial design is shown in Figure 1. The key features are that, after a patient has been assessed as likely to benefit from an exercise intervention, their referral is to the project research assistant who will allocate the patient to one of four conditions on the basis of previous independent randomisation. These are: 1) GP gym-based referral (GPGR, the treatment as usual control); 2) GP gym-based referral plus web tool (GPGR + WEB); 3) sport referral at Surrey Sports Park (SPR); and 4) sport referral at Surrey Sports Park plus web tool (SPR + WEB). After obtaining informed consent patients attend a 12-week exercise programme (sport or gym) and their activity levels and sporting participation are monitored again at 6 months and 12 months after starting the exercise programme. Pending ethical approval the intention is to commence recruitment in the early autumn of 2013 for a period of 9 months.

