#### Intervention effectiveness

For the primary outcome of activity, and assuming normal variable distributions, the intervention arms will be compared to the control arm using *t*-tests and one-way analysis of covariance using study arm as the between-subjects factor and baseline activity scores as the covariate (following Senn,
[36]). Similar analyses will be conducted for the secondary outcome variables and in all cases effect sizes reported. Where variable distributions do not initially permit the use of parametric inference tests, variables will be subjected to mathematical transformation to achieve normality. In cases where transformations are not effective, non-parametric tests on difference scores will be used. Differences between arms in the proportions achieving more than 10 mmHg reductions in blood pressure will be assessed using chi-square tests.

Analyses will be conducted on a per-protocol basis. Interim assessment of the efficacy of the interventions will be made at 6 months.

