#### Moderator and mediator analyses

To attempt to establish how the interventions work and for whom, we will conduct a series of mediation and moderation analyses following established bootstrapping procedures outlined in
[37]. Putative moderators will include participant demographic factors, baseline intentions to engage in activity, feelings of self-efficacy and autonomy.

Potential mediators will include number of implementation intentions formed (in web-tool arms), frequency and intensity of use of the web-based tool, enjoyment of the 12-week exercise programme, attendance at the programme, perceptions of autonomy over exercise during the training programme, and intentions to exercise post-exercise programme.

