## Discussion

This randomised controlled trial compares GP referral to sport-based exercise with referral to the more conventional gym-based exercise programme. It hypothesises that enjoyment, choice and therefore some degree of control might result in greater persistence. It is needed because, currently, such a small proportion of people referred for exercise persist. The challenges for this trial include recruiting sufficient numbers to the trial, and matching those who are recruited to appropriate exercise-based interventions. We need to recruit 2,000 patients and we need to provide those allocated to sports-based exercise activities at a time and of a type that they might opt to participate in. There are many uncertainties as to the feasibility of this, which will be tested in the course of this study.

Further parallel work is required to explore change in vascular risk and the potential cost effectiveness of sport-based exercise interventions. The trial is not looking at overall cardiovascular risk, or change in risk score (such as Framingham or QRisk score), nor at major cardiovascular outcomes and death. The former may be required in order to carry out a cost-effectiveness analysis. The latter would provide data on the safety of referral for sport-based exercise programmes and also about any change in health outcomes, though the scale of the trial and duration of follow-up would not provide sufficient data for any difference to be detectable between arms.

The theoretical framework around the importance of enjoyment and control potentially leading to greater persistence with sport-based, compared to gym-based, exercise may be challenged if we find no difference between arms.

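### Per-protocol is the only analysis population named, and it is undefined, in a superiority trial of interventions meant to change persistence

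*Protocol article*

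**What the plan says.** The Intervention effectiveness section sets out the primary comparison: "the intervention arms will be compared to the control arm using *t*-tests and one-way analysis of covariance using study arm as the between-subjects factor", with baseline activity as covariate. Similar analyses follow for the secondary outcomes. The section then states, without qualification: "Analyses will be conducted on a per-protocol basis". The article mentions no as-randomised or intention-to-treat population, and it does not say what a participant must do to count as per-protocol.

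The question is one of superiority. Research questions and hypotheses describes interventions "intended to promote sustained and increased levels of physical activity over a period of 12 months" and calls them superior if they exceed gym referral by 20 MET-minutes per week. The Discussion gives the mechanism: "It hypothesises that enjoyment, choice and therefore some degree of control might result in greater persistence". It also gives the motive: "It is needed because, currently, such a small proportion of people referred for exercise persist". Moderator and mediator analyses lists among the potential mediators "enjoyment of the 12-week exercise programme, attendance at the programme, perceptions of autonomy over exercise during the training programme". In Methods/design, activity is "monitored again at 6 months and 12 months after starting the exercise programme".

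**The concern.** Randomisation makes the arms comparable at allocation. A per-protocol set is formed afterwards, from behaviour that allocation may have altered. Here that is more than a general worry, because the interventions are hypothesised to work by keeping people going and the article treats attendance as a possible step between allocation and outcome. Removing people on that step compares differently selected groups and leaves out some of the people whose number the interventions are meant to reduce.

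The planned covariate does not cure this. Baseline activity is one measured characteristic, in a population already screened as inactive or moderately inactive. Staying with a programme also depends on motivation, health, time and the experience of the programme itself.

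What is at stake is the primary comparison. The planning effect is only 0.125 SD, so a modest selection bias could create or hide a result of that size.

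**Working it through.** **Is it a stated choice or an omission?** The sentence affirmatively names a population, directly after the primary and secondary comparisons, and nothing elsewhere in the article offsets it. It is therefore not a detail left to an analysis plan. A plan that followed the article would carry it forward.

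**How large could the bias be?** The plan gives no figure to reproduce here, because it states neither adherence rates nor a per-protocol definition. The only input from the article is the benchmark, the effect size of 0.125 in Sample size and power calculations and randomisation. Everything else below is assumed.

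*Model.* There is no true treatment effect. The outcome is normal with SD 1. A latent tendency to adhere has correlation rho with the outcome, and the top fraction p of each arm is retained. The mean outcome among those retained is then shifted upward by

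shift = rho × φ(z_p) / p,

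where z_p is the normal quantile that leaves a fraction p above it. The bias is the shift in the intervention arm minus the shift in the control arm.

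*Values of φ(z_p)/p:* 0.644 for p = 0.60; 1.058 for p = 0.35; 0.570 for p = 0.65; 0.798 for p = 0.50.

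| Hypothetical retention (intervention v control) | Difference in φ(z_p)/p | rho 0.2 | rho 0.3 | rho 0.5 |
|---|---|---|---|---|
| Gym + web 35% v gym 60% | 1.058 − 0.644 = +0.414 | +0.083 | +0.124 | +0.207 |
| Sport 65% v gym 50% | 0.570 − 0.798 = −0.228 | −0.046 | −0.068 | −0.114 |
| Sport 60% v gym 50% | 0.644 − 0.798 = −0.154 | −0.031 | −0.046 | −0.077 |
| Equal retention, equal rho | 0 | 0 | 0 | 0 |

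The arm that retains fewer people looks better, so exchanging the rates between arms reverses the sign. At rho = 0.3 the first row gives 0.124/0.125 = 99% of the planning effect, and the second gives 0.068/0.125 = 54% in the opposite direction.

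Equal retention is not a safeguard if selection differs in strength. With 60% retained in both arms but rho 0.2 in control and 0.4 in the intervention arm, the bias is 0.644 × (0.4 − 0.2) = 0.129 SD.

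*Allowing for the planned covariate.* Rho should be read as the correlation left after adjusting for baseline activity. The shift is then approximately in units of the residual SD. If baseline and 12-month activity correlated at 0.5 (assumed), the figures in units of the raw SD would be multiplied by √(1 − 0.5²) = 0.87, so 0.124 becomes about 0.11. The bias shrinks but does not vanish.

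**The case against.** The strongest reply is that much of the alarm depends on a definition the article never gives. Four stronger readings are tempting, and the document supports none of them.

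- **Only self-selected persisters are compared.** No such rule is stated. Attendance and logins are described under Measures as exposure, with no threshold for inclusion. Using them as mediators requires them to vary among those analysed.
- **The persistence effect is conditioned away altogether.** The programme lasts 12 weeks and the outcome is at one year. If per-protocol means completing the course, people who lapse later stay in and later persistence is still compared. Only drop-out within the course would be conditioned on.
- **People who never start are not followed up.** Timing follow-up from the start of the programme leaves their date undefined, but it does not say they go uncontacted. The fuller protocol may deal with this.
- **The bias has been shown to match the planning effect.** It has not. The gym + web figure supposes that per-protocol requires both attendance and tool use, which appears nowhere. Other equally hypothetical rates give less, or nothing.

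The article also mixes the words efficacy and effectiveness, so the intended estimand is less clear than it might be. And the Background remark that "the absolute health risk reduction was small due to patients failing to maintain activity levels over time" concerns earlier studies of gym referral, so it is context and not evidence about this trial's analysis.

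All of this limits the size and wording of the point but does not remove it. Whichever usual definition is meant, some people are excluded for post-randomisation behaviour, no as-randomised comparison stands beside it, and an efficacy label does not make the comparison unbiased.

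**Conclusion.** The point holds, and it should be corrected before analysis. Followed as written, the plan answers a superiority question in an undefined per-protocol set alone, with exclusions that depend on behaviour the interventions are hypothesised to change. That conclusion rests on the wording and does not depend on the arithmetic.

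The size is illustrative. The two main scenarios give about 0.05 to 0.2 SD, in either direction according to which arm retains fewer people, beside a planning effect of 0.125 SD. Smaller adherence gaps give less (0.03 SD at 60% v 50% with rho 0.2), and equal adherence with equal selection gives zero. The retention rates, rho and the form of the per-protocol set are all assumptions. Neither the actual size nor the direction of the bias can be known from the article.

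**What to change.** Replace the per-protocol sentence with one stating that the primary analysis includes all randomised participants in the arm to which they were allocated, whatever their attendance or use of the web tool.

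Send the 6- and 12-month questionnaires to non-starters and drop-outs as well. Because follow-up is timed from starting the programme, give non-starters a stated date, for example one counted from randomisation.

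Keep a per-protocol analysis as a labelled secondary analysis, with its attendance and web-use criteria defined in advance for each arm. A repeated-measures model using the 6- and 12-month scores is an option, but it is not needed to cure this point.

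The cost is small: revised wording in the protocol and any analysis plan, and some extra follow-up by a questionnaire that is already online. The article reports data collection as continuing, so the change was still practicable when it was published. The real downside is that the estimate may be diluted relative to the effect among people who adhere, which the secondary analysis can explore with its limits stated.

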#### Moderator and mediator analyses

To attempt to establish how the interventions work and for whom, we will conduct a series of mediation and moderation analyses following established bootstrapping procedures outlined in
[37]. Putative moderators will include participant demographic factors, baseline intentions to engage in activity, feelings of self-efficacy and autonomy.

Potential mediators will include number of implementation intentions formed (in web-tool arms), frequency and intensity of use of the web-based tool, enjoyment of the 12-week exercise programme, attendance at the programme, perceptions of autonomy over exercise during the training programme, and intentions to exercise post-exercise programme.

### Ethics

The trial has received a favourable ethical opinion by the London Bloomsbury National Research Ethics Service committee (13/LO/1170) and commenced recruitment in October 2013. To date, ten practices have expressed an interest in identifying potential participants for the trial.

## Discussion

This randomised controlled trial compares GP referral to sport-based exercise with referral to the more conventional gym-based exercise programme. It hypothesises that enjoyment, choice and therefore some degree of control might result in greater persistence. It is needed because, currently, such a small proportion of people referred for exercise persist. The challenges for this trial include recruiting sufficient numbers to the trial, and matching those who are recruited to appropriate exercise-based interventions. We need to recruit 2,000 patients and we need to provide those allocated to sports-based exercise activities at a time and of a type that they might opt to participate in. There are many uncertainties as to the feasibility of this, which will be tested in the course of this study.

Further parallel work is required to explore change in vascular risk and the potential cost effectiveness of sport-based exercise interventions. The trial is not looking at overall cardiovascular risk, or change in risk score (such as Framingham or QRisk score), nor at major cardiovascular outcomes and death. The former may be required in order to carry out a cost-effectiveness analysis. The latter would provide data on the safety of referral for sport-based exercise programmes and also about any change in health outcomes, though the scale of the trial and duration of follow-up would not provide sufficient data for any difference to be detectable between arms.

The theoretical framework around the importance of enjoyment and control potentially leading to greater persistence with sport-based, compared to gym-based, exercise may be challenged if we find no difference between arms.

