### Sample size and power calculations and randomisation

Davies and colleagues report a meta-analysis of internet-based exercise intervention studies which suggests an average effect size of d = 0.14
[16]. A Cochrane review of general interventions to promote activity among inactive adults reports an average SMD = 0.28, but notes considerable heterogeneity in effects sizes
[4]. In the case of internet interventions aimed at reducing blood pressure, effects sizes of the order of SMD = 0.27 and 0.17 for systolic and diastolic blood pressure, respectively (equating to drops of 3.8 and 2.1 mmHg, respectively), have been identified in a recent meta-analysis
[35]. Based on these analyses, an effect size of 0.125 can be assumed for comparing means of MET-minutes per week and mmHg between the intervention and control arms (equinumerous) for a two-arm study. With this effect size, if each arm consists of 500 subjects, a power of 80% is obtained for a two-sided statistical contrast to show statistical significance, at the 5% level, of the difference of the means of the two arms with respect to these outcome variables. It is therefore decided that there will be 500 subjects in each of the four arms of the present study.

Block randomisation is to be conducted by the University of Surrey’s Clinical Research Centre. Participants cannot be blinded to the nature of the intervention they are receiving and for reasons of monitoring and contacting participants the research assistant also cannot be blinded. The primary analyst will be blinded to participant allocation.

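### The Discussion treats a null result as a challenge to the enjoyment-and-control theory, but the named arm comparison has about 51% power for the planning effect, so most such nulls would be inconclusive if that effect is real

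*Protocol article*

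**What the plan says.** The Discussion ends by linking a null result to the theory behind the sport programme, namely that enjoyment and control make people keep exercising. It says that this framework for sport-based, "compared to gym-based, exercise may be challenged if we find no difference between arms". It does not define what finding no difference means.

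The sample size section supplies the planning effect: "an effect size of 0.125 can be assumed for comparing means of MET-minutes per week and mmHg between the intervention and control arms". The test is a "two-sided statistical contrast to show statistical significance, at the 5% level", and the section asserts that "if each arm consists of 500 subjects, a power of 80% is obtained". The calculation is for a comparison "between the intervention and control arms (equinumerous) for a two-arm study", and the 500 is then applied to each of the four arms.

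Under Intervention effectiveness, "the intervention arms will be compared to the control arm using" t-tests and a one-way analysis of covariance on baseline activity. Effect sizes are to be reported, and the analyses are per protocol. The section on moderators and mediators lists "enjoyment of the 12-week exercise programme, attendance at the programme, perceptions of autonomy over exercise during the training programme" among the potential mediators. The research questions section adds a superiority threshold of 20 MET-minutes per week over gym referral. It gives no standard deviation and does not tie the threshold to a confidence limit.

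**The concern.** A null result bears on a theory only to the extent that the data exclude the effect the theory predicts. Here the predicted size is the planning effect of 0.125 SD, and the comparison named in the analysis section is one arm of 500 against another. If that comparison often misses a true effect of 0.125 SD, a non-significant result says little about whether the theory is wrong.

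The stated 80% power makes the sentence look safer than it is. A null has probability 0.95 if the true effect is zero. At 80% power it has probability 0.20 if the planning effect is real, so a null would favour zero by 0.95/0.20 = 4.75. At the recomputed power the ratio is 0.95/0.49, about 1.9. A reader who trusts the article would therefore give a null much more weight than it can carry, and sport referral and its rationale could be marked down on data still compatible with the benefit that the trial was sized to find.

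**Working it through.** **Inputs.** From the sample size section: standardised effect d = 0.125, two-sided alpha 0.05, n = 500 per arm, stated power 80%. From Intervention effectiveness: each intervention arm against control, by t-test and by ANCOVA on baseline activity. Not given, and assumed here: the baseline–outcome correlation r (range 0.3 to 0.7) and loss to analysis (20%).

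**1. The plan's own figure.** Power = Φ(d√(n/2) − 1.96).
- d√(n/2) = 0.125 × √250 = 1.976, so power = Φ(0.0165) = 50.7%. The exact noncentral t gives 50.6%. The miss rate is about 49%.
- The stated 80% does not reproduce. It would need n = 2(1.960 + 0.842)²/0.125² = 1,005 per arm.
- One-sided 5% gives 63.0%. The figure of 500 does match a one-sample formula: (1.960 + 0.842)²/0.125² = 502.3, with 79.8% power at 500.

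**2. Baseline adjustment and loss.** For ANCOVA, d is replaced by d/√(1 − r²).

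| r | Power, 500 per arm | Power, 400 per arm (20% loss) |
|---|---|---|
| 0 (t-test) | 50.7% | 42.4% |
| 0.3 | 54.5% | 45.7% |
| 0.5 | 62.6% | 53.2% |
| 0.7 | 79.0% | 69.7% |

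With 500 per arm, 80% power needs r = √(1 − 500/1,004.7) = 0.71.

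**3. What a null would exclude.** The unadjusted 95% half-width is 1.96 × √(2/500) = 0.124 SD.
- The upper limit falls below 0.125 only if the estimate is below 0.125 − 0.124 = 0.001 SD. An estimate of exactly zero just excludes the planning effect. Essentially any positive non-significant estimate does not.
- If the true effect is zero, the interval excludes 0.125 SD with probability Φ(0.001/0.0632), about 51%.
- If the true effect is 0.125 SD, a null whose interval excludes 0.125 has probability about 0.025. Out of a total null probability of 0.493 that is about 5%, so about 95% of nulls would be inconclusive.
- With ANCOVA at r = 0.5 the half-width is 0.124 × √0.75 = 0.107 SD, and non-significant estimates between 0.018 and 0.107 SD remain inconclusive.

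**4. The pooled contrast.** Both sport arms against both gym arms, 1,000 v 1,000 with no interaction:
- Power = Φ(0.125 × √500 − 1.96) = 79.8%, or 70.5% with 20% loss (800 v 800).
- The half-width is 0.088 SD, so non-significant estimates above 0.125 − 0.088 = 0.037 SD still include 0.125.

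**The case against.** The strongest reply is that there is no rule here to correct. The sentence says only that the framework may be challenged. It names no test and commits to no conclusion. A reader might infer that the protocol would formally count a non-significant test as evidence against the theory, but the text does not support that. What stands is narrower: the sentence invites the inference, and its only condition is that no difference is found.

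A reader might also infer that significance tests are the only tools planned. They are not. Effect sizes are to be reported, a 20 MET-minute superiority threshold is set, and bootstrapped mediation analyses are planned. None of these says how large a benefit must be excluded before the theory is in doubt.

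The remark compares sport with gym, which could mean the pooled contrast, and pooling would bring the miss rate down to about 20% with full retention and no interaction. That is a fair point. However, the analysis section names only comparisons of intervention arms with the control arm.

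Much of the size of the problem comes from the faulty power statement. With 1,005 per arm the miss rate would be 20%. Even then the half-width would be 1.96 × √(2/1,005) = 0.087 SD, and a non-significant estimate between about 0.038 and 0.087 SD would not exclude 0.125. The point shrinks but does not vanish.

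A condensed article may leave confidence-interval rules to an analysis plan that is not shown, so their absence alone would not be a finding. The point rests on what the article states.

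Two further readings go too far. Miss rates for 20 MET-minutes would rest wholly on an assumed SD: 20 equals 0.125 SD only if the SD is 160 MET-minutes, and none is given. Nor should greater enjoyment in the sport arms be a precondition for challenging the theory. The article makes sport's added enjoyment part of its rationale, so a failure to raise enjoyment could itself count against the framework.

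**Conclusion.** The concern holds in a limited form. On the article's own inputs, the arm-against-control t-test has about 51% power for 0.125 SD and misses it about 49% of the time, with full retention and no adjustment. Across the assumed correlations of 0.3 to 0.7, ANCOVA brings the miss rate to between 46% and 21% with 500 per arm, and to between 54% and 30% with 400 per arm. A non-significant positive estimate from the unadjusted comparison cannot exclude the planning effect. The Discussion sentence therefore suggests an inference that the named comparison cannot generally support. A pooled contrast would ease this but not remove it. The root error is the 80% power figure, which should be restated in its own right. The change proposed here is worth making but is not critical, because the sentence is hedged and governs no decision.

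**What to change.** In the analysis plan or the next protocol update, before the arms are compared, replace the Discussion sentence with wording of this kind:

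*The enjoyment-and-control framework will be regarded as challenged only if the upper limit of the two-sided 95% confidence interval for the baseline-adjusted sport minus gym difference in MET-minutes per week at 12 months lies below 0.125 SD, the planning effect. A non-significant result whose interval includes 0.125 SD will be reported as inconclusive.*

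State which contrast this refers to: SPR against GPGR, or both sport arms against both gym arms. If pooled, state the no-interaction assumption. State also which SD defines the 0.125. Report the planned enjoyment and autonomy results alongside as context, not as a condition. Correct the power statement separately.

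The cost is a few sentences, with no extra patients or data. The downside is that some null results must be called inconclusive: for the unadjusted single-arm contrast, about half of them even if the true effect is zero.
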